### Study procedures

#### Recruitment

The study team will establish Community Research Support Groups (CRSG) in all the study districts following the model adopted by the HIV Incidence Provincial Surveillance System (HIPPS) in the uMgungundlovu district [44]. Data collection will be preceded by building strong community relationships through extensive community engagement and advocacy with local stakeholders including traditional leaders, DREAMS implementing partners, other public, private and NGO service providers within the study districts related to education, psycho-social support, socio-economic support as well as health services. The CRSG will provide a forum for the engagement between researchers and community members, preserving the community’s best interests and ensuring that the study team are aware of any concerns about the research. As with HIPSS, the CRSG will provide input into the informed consent procedures, questionnaire design and administration of the surveys [44].

Following community sensitisation, study staff will approach households included in the sample and introduce the study to the household residents. All individuals in the household who meet the eligibility criteria and are available to be interviewed will be asked to participate in the study. Those who do not wish to participate in the study will be asked to provide feedback about their decision for declining in order to characterise the impact of refusal on the study’s outcomes. Those who agree to participate will be asked to designate a location, either inside or outside their residence, where the survey instruments can be administered and biological samples collected privately.

Participants in the study will be compensated nominally for their time with a gift to the value of between 2 and 3 United States Dollars. A Parent/guardian of AGYW aged 12–17 years will be asked to complete a caregiver questionnaire (See addional file 2). No biological samples will be collected from caregivers, defined as a parent or guardian who is primarily responsible for the pre-selected AGYW’s welfare, specifically the person who prepares meals, seeks medical attention for the AGYW in the case of illness and otherwise cares for the AGYW.

In the situation where the respondent is 17 years or younger and does not live with any caregiver (a child-headed household), a caregiver survey will not be administered. In instances where no caregiver survey is administered, additional questions from the caregiver questionnaire are included in the AGYW questionnaire. In the case of a person being a caregiver to more than one study participant, this caregiver will be required to complete the relevant questions for all AGYW residing within the household. If the caregiver is not present at the time the interviewer accessed the household, the interviewer will obtain the contact details of the caregiver, if available, and schedule a return visit at an agreed upon date and time to obtain informed consent and conduct the interview.

### Data collection

Each participant is assigned a unique study number linked to the questionnaire and administered by study staff using a personal digital assistant (PDA). Study staff with training in phlebotomy will collect two micro-containers of whole blood for DBS and plasma specimens, whilst participants will be guided to collect a VVSS. Blood will be drawn from finger pricks, considered relatively non-invasive and not expected to negatively affect participation. Blood specimens will be stored in sterile containers and logged onto a laboratory tracking sheet. The specimens will then be couriered to a laboratory in KZN for testing. The blood is shipped daily from the study sites to the laboratory. The Standard Operating Procedure for taking blood is based on the protocols of the South African National Department of Health (NDoH) for taking blood for the HIV Polymerase chain reaction (PCR) test [45].

Study staff will administer a questionnaire to obtain:
Socio-economic status of the household, including income, food security and location (urban or rural) and proximity to national roads, clinics and schools.Demographic information of study participants including age, gender, marital status, occupation, employment and educational status.Psycho-social information, including HIV knowledge, attitudes, perceived risk, self-efficacy and social norms related to HIV and AIDS, as well as depression indicators.Academic milestones of study participants, including academic progress and school completion.Behavioural information including age of sex initiation, partner characteristics (including age; number; type (regular/casual); circumcision status, HIV status); partner concurrency; condom use; engagement in transactional sex, substance (including alcohol) abuse and prevalence of intimate partner violence will be collected.Health seeking behaviour, including HIV testing (date of last HIV test, HIV test results) and HIV treatment (initiation date); STIs testing and treatment and contraceptive use.Exposure and engagement with DREAMS interventions.

### Access to health care

All study participants will be provided with a barcoded card and informed that they have an opportunity to access their HIV test results. Participants will be notified of the name of the clinic where their results will be sent. All participants’ laboratory HIV and pregnancy results will be sent to the nearest NDoH primary health clinic two weeks post collection of the biological samples for participants to access using their barcoded card. Participants will be encouraged to visit the clinic to obtain their results and receive appropriate counselling and referrals to access care and treatment.

HTS will be made available to study participants and household members wanting to know their HIV status immediately. They will be tested upon completion of data collection by the field worker using a rapid HIV test guided by SA NDoH HIV testing protocols [44]. Referrals to care, support and treatment will be made if required. Records of individuals referred for test results, treatment and care will be kept to monitor uptake of services.

### Outcomes and analysis

The primary outcome will be HIV incidence. The analysis will determine whether the aim of an HIV-incidence reduction of 40% at 2 years post implementation of the DREAMS programme in a ‘real world, non-trial setting’ was realised.

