### Primary hypothesis

The DREAMS initiative will collectively reduce HIV incidence amongst AGYW by 25% by the end of year one of its implementation, and by 40% by the end of year two in those districts where DREAMS programmes were implemented.

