### Statistical considerations and sample size calculation

The sample size of 8000 per survey in the two KZN districts will have 80% power to detect a reduction of 40% in the HIV incidence rate at the 5% significance level given a false recent rate (FRR) of 0.01%, HIV prevalence of 25%, and an initial HIV incidence rate of 4 per 100 person years (py) [33]. A sample size of 10,500 per survey in the two GP districts will have 80% power to detect a 40% reduction in HIV incidence given a FRR of 0.01%, HIV prevalence of 25% and baseline incidence of 3/100py amongst AGYW aged between 12 and 24 years [8].

The aforementioned sample size calculations are based on detecting change in incidence and not the precision of individual estimates. However, the sample size of 8000 in KZN is adequate to estimate an HIV incidence rate of 4% with a coefficient of variation of 12%, corresponding to a confidence interval of (3.1–4.9%). The sample size in Gauteng of 10,500 will allow us to estimate the HIV incidence rate of 3% with a coefficient of variation of 12% and confidence interval of (2.28–3.72).

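### The stated 80% power is for rejecting no change when the true fall is 40%; it does not cover the promised conclusion that a 40% reduction was achieved

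*Protocol article*

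**What the plan says.** Three places in the protocol article set the question and the power.

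- *Primary hypothesis*: DREAMS is to reduce incidence among adolescent girls and young women "by 25% by the end of year one of its implementation, and by 40% by the end of year two".
- *Outcomes and analysis*: "The analysis will determine whether the aim of an HIV-incidence reduction of 40% at 2 years post implementation" was achieved. Here 40% is the threshold to be judged.
- *Statistical considerations and sample size calculation*: 8,000 per survey in KwaZulu-Natal (KZN) give "80% power to detect a reduction of 40% in the HIV incidence rate at the 5% significance level", with a starting incidence of 4 per 100 person-years. For Gauteng, "A sample size of 10,500 per survey in the two GP districts will have 80% power to detect a 40% reduction in HIV incidence", from a baseline of 3 per 100 person-years. The section adds that sizing rests on finding a change, not on the precision of each estimate. It then gives a coefficient of variation (CV) of 12% for each province's incidence.

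Two further statements bear on the size of the problem. *Study design* plans one cross-sectional survey in 2017/2018. *Study aim* takes the baseline mainly from existing studies and quotes their confidence intervals.

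**The concern.** Power to detect a 40% reduction is the chance of rejecting no change when the truth is 40%. The hypothesis and the analysis section ask whether the reduction reached 40%. Rejecting no change leaves that open, because the same data may also fit a much smaller fall. The article gives no power or precision for the estimated reduction itself, so a reader will naturally attach the 80% to the target question.

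The evaluation is meant to inform expansion of the programme. A significant fall could be presented as the target met when the interval reaches down to about 12%, or an estimate somewhat below 40% could be presented as the target missed when the data do not exclude 40%.

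**Working it through.** **Inputs from the article.** CV 12% in each province; baseline 4 (KZN) and 3 (Gauteng) per 100 person-years; reduction 40%; 5% level. Sidedness, mean duration of recent infection and design effect are not stated.

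**Step 1: the plan's own figures.**

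- Intervals: 4 × (1 ± 1.96 × 0.12) = 3.06 to 4.94, and 3 × (1 ± 1.96 × 0.12) = 2.29 to 3.71 (2.28 to 3.72 with multiplier 2). These match the stated 3.1–4.9 and 2.28–3.72.
- Power against no change, KZN, difference scale: the difference is 4 − 2.4 = 1.6. If both surveys have CV 12%, SE = 0.12 × √(4² + 2.4²) = 0.560 and power is 81.5%. If the second CV grows to 0.12/√0.6 because fewer recent infections are found, SE = √(0.2304 + 0.1382) = 0.607 and power is 75% two-sided or 84% one-sided.
- Using the variance of a recency-assay incidence estimator under simple random sampling, an assumed mean duration of recent infection of 118 days gives 79.0% (KZN) and 78.4% (Gauteng); 130 days gives 82.7% and 82.2%.

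So 80% cannot be reproduced exactly without the unstated inputs, but it fits a null of no change under plausible values. It is not shown to be wrong.

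**Step 2: precision of the reduction.** Assume two independent surveys of equal size. For a true reduction r, the SE of the log rate ratio is √(0.12² + 0.12²/(1 − r)).

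- At r = 0.40: √(0.0144 + 0.0240) = 0.196.
- Expected 95% CI for the reduction: 1 − 0.6 × exp(±1.96 × 0.196) = 11.9% to 59.1%.
- Provinces pooled, same true reduction: SE = 0.196/√2 = 0.139, CI 21.3% to 54.3%.
- Baseline treated as known without error: SE = √0.0240 = 0.155, CI 18.7% to 55.7%.

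**Step 3: chance that the interval settles the target** (per province, two surveys, null at a rate ratio of 0.6). With z = |ln((1 − r)/0.6)|/SE, the chance that the interval excludes 40% on the correct side is Φ(z − 1.96).

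| True reduction | Interval wholly below 40% | Interval wholly above 40% |
|---|---|---|
| 0% | 85% | 0% |
| 10% | 64% | 0% |
| 25% | 23% | 0.1% |
| 50% | 0.2% | 14% |
| 60% | 0% | 44% |
| 70% | 0% | 79% |

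Example at 25%: SE = √(0.0144 + 0.0192) = 0.183; z = 0.223/0.183 = 1.217; Φ(−0.743) = 0.23.

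**Step 4: one survey against an external baseline.** The SE of the log baseline is ln(upper/lower)/3.92; the survey contributes a variance of 0.0240 at a true 40% fall.

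- uMgungundlovu, 15–19 years, 4.63 (3.29–6.52): SE 0.174, combined 0.233, CI 5.2% to 62.0%.
- uMgungundlovu, 20–24 years, 4.00 (2.74–5.85): SE 0.193, combined 0.248, CI 2.5% to 63.1%.
- National 2012, 15–24 years, 2.54 (2.04–3.04): SE 0.102, combined 0.185, CI 13.7% to 58.3%. This reflects sampling error only; the figure is neither specific to the districts nor contemporary with the start of the programme.

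These are illustrations: they set a provincial survey CV against a baseline from one district and age band, or from the whole country.

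**The case against.** The strongest reply is that this is one sentence in a condensed article. *Study objectives* frames the primary objective as measuring the change in incidence, which agrees with the sample size section, and that section openly says it was sized for change. How the estimate will be set against the target may be laid down in a full protocol or analysis plan that is not shown. The *Discussion* already concedes an estimated baseline and limited attribution.

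Much of this stands. No passage says that the point estimate will decide, or that a significant fall will be reported as 40% achieved. The absence of a decision rule is therefore not the point. What remains is that the article states one power and promises a different conclusion. A later rule cannot change the precision implied by a 12% CV, and the listed limitations do not mention the 40% threshold.

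A reader might also infer more than the article supports:

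- *That the study has 80% power for any fall.* It applies at a true 40%; for a true 25% fall the same calculation gives about 35%.
- *That judging by the point estimate, or by the lower limit, exposes a shortage of participants.* At a true 40%, an estimate of 40% or more occurs half the time, and a lower limit above 40% occurs 2.5% of the time, at any sample size. Only the interval width and the chances away from 40% say anything about this sample.

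**Conclusion.** The point holds as a mismatch between stated power and stated conclusion. The 80% belongs to a test of no change at a true 40% fall. For the target question, the article's own CV and two equal independent surveys give an expected interval of about 12% to 59% per province. Even the favourable cases, pooled provinces (21% to 54%) or a baseline known without error (19% to 56%), leave attainment of 40% unresolved when the truth is near it.

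It would go too far to say that the study cannot address the target at all. It would probably show the target missed if there were almost no reduction, and exceeded if the reduction were about 70% or more. Between those extremes it would often be inconclusive.

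The design actually described, one survey against outside data, has its own interval: about 3% to 63% with the less precise of the two quoted district baselines. The figures assume that the 12% CV already reflects the survey design, which the article does not say; if it does not, the intervals are wider.

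**What to change.** - *Outcomes and analysis*: make the primary analysis the estimated percentage reduction with its 95% confidence interval, carrying the uncertainty of the external baseline, tested against no change. Describe the 40% target as shown to be met or missed only when the interval excludes 40%, and otherwise as inconclusive. A programme that truly achieved about 40% would then usually be reported as inconclusive, not as a failure.
- *Primary hypothesis*: align the wording, so that 40% reads as the programme's target and not as something the 80% power can confirm.
- *Statistical considerations and sample size calculation*: say that the 80% refers only to the test against no change at a true 40% reduction. Add the expected interval for the reduction, computed for the design in use (one survey against the chosen external baseline) and not for two equal surveys.

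The cost is wording and a short recalculation. No extra participants are needed. The claim becomes less favourable, since the article would concede that the target question may well end inconclusive.

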### Analysis of the primary objective

The study will use the Limiting antigen Avidity (LAg) Enzyme Immuno-Assay (EIA) to estimate recent HIV infection from the cross-sectional survey. The LAg EIA has been shown to be a reliable method of generating cross-sectional incidence estimates [46].

### Analysis of secondary objectives

**Measure HIV prevalence, and proportion on ART and ART naïve with detectable and undetectable HIV-1 viral load**: HIV prevalence will be expressed as the proportion testing HIV positive, where the denominator is all who provided a blood sample for HIV testing and had a conclusive result. The proportion of HIV positive AGYW on ART and those not on ART who have detectable or undetectable viral loads will be determined through laboratory tests that have a dynamic range of 20 to 10 million copies/ml. HIV-1 viral load data and Antiretroviral (ARV) drug measurement data will be used to determine the proportion of HIV infected persons on ART and ART naïve with detectable and undetectable viral loads. Participants who achieve viral suppression will be defined as those with a viral load < 1000 copies/ml. Estimated prevalence will take the survey design and sampling weights into account.

**Measure prevalence of pregnancies and sexually transmitted infections (STIs)**: Pregnancy and STIs (overall and individual diseases: (HBV, HSV-2, Syphilis, HPV, *C.trachomatis, N. gonorrhoea, T. vaginalis* and *M. genitalium*) will be calculated with 95% Confidence Interval (CIs). Pregnancy prevalence is defined as the proportion of AGYW testing positive for pregnancy from their blood samples, where all AGYW tested for pregnancy in this study is the denominator. Individual STI prevalence is calculated as the number of individuals testing positive for a particular STI, divided by all AGYW who were tested for STIs. Secondary analysis will be disaggregated by age, gender, marital status, occupation, employment status and educational attainment as well as other socioeconomic indicators and exposure to DREAMS interventions. All estimates will take the survey design and sampling weights into account.

**Measure risky sexual behaviour (e.g. number of [concurrent, lifetime, age-disparate] sexual partners, condom use, age of sexual debut), gender norms, intimate partner violence (including gender-based violence), and selected academic performance indicators (e.g. academic progress, school completion, assertive behaviour, participation in school and sport)**: The prevalence of risky sexual behaviour, gender norms and episodes of intimate partner violence (IPV) within the past year will be calculated with 95% CIs. IPV is assessed using behaviourally specific items developed by the World Health Organisation, and modified and used extensively in South Africa [47]. Five items ask about past experiences of physical violence from an intimate partner, whilst three items ask about sexual IPV in the previous year. Responses to each item are “never”, “once”, or “more than once”. A positive answer to any of the items leads to a woman being classified as having experienced IPV. Only women reporting having a boyfriend, husband, or having had sex with a man are asked these questions. Gender norms are measured using the gender equitable men (GEM) scale, this scale consists of 6 items relating to norms about male-female relationships and interactions. The scale asks respondents how much control their partners have over them in their relationships in relation to the clothes they wear, decisions made in the relationship and who they can spend time with outside of their relationship. Responses to each item are based on a Likert-type scale with responses ranging from strongly agree to strongly disagree. The scale items will be summed and a mean score calculated. Secondary analysis will be disaggregated by age, HIV and STI status and other socio-economic and academic indicators and exposure to DREAMS interventions.

**To measure the impact of economic empowerment, socio-economic status of their family, and selected parent/guardian/caregiver indicators have had on both the HIV incidence among AGYW and prevalence of GBV/IPV perpetrated against AGYW**: Composite scores will be created for AGYW using multiple correspondence analyses (MCA), taking the survey design and sampling weights into account.

**To measure the exposure to the DREAMS programme including condom promotion and provision (male and female); HTS and linkage to care; GBV prevention and post violence care and support; comprehensive sexual reproductive health rights (SRHR) services; social asset building interventions; school-based HIV and violence prevention; community mobilization and changes in social norms; parenting/caregiver programmes:** Composite scores will be created for AGYW and caregivers using self-reported data on their exposure to DREAMS activities. The mean score between AGYW exposed to DREAMS interventions and those who haven’t, will be compared using linear regression and by taking the survey design and sampling weights into account.

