### Study objectives

The primary objective of this study is:
Measure the change in HIV-1 incidence following implementation of the DREAMS suite of interventions within a ‘real world, non-trial setting’.

The secondary objectives are to:
Measure HIV prevalence, and proportion of HIV positive AGYW on ART and ART naïve with detectable and undetectable HIV-1 Ribonucleic Acid (RNA) viral load.Measure prevalence of pregnancies and sexually transmitted infections (STIs) including Hepatitis B virus (HBV), Herpes simplex virus type 2 (HSV-2), syphilis, human papillomavirus (HPV*), Chlamydia trachomatis*, *Neisseriae gonorrhoea*, *Trichomonas vaginalis* and *Mycloplasma genitalium.*Measure risky sexual behaviour, specifically, the number of past year sexual partners, condom use, and age-disparate and concurrent partnering.Measure the prevalence of intimate partner violence.Measure performance on selected academic milestones (e.g. academic progress, school completion rates).Measure the economic empowerment of AGYW, socio-economic status of their family and selected parent/guardian/caregiver indicators.To measure the exposure to the DREAMS programme including condom promotion and provision (male and female); HIV testing services (HTS) and linkage to care; GBV prevention and post violence care and support; comprehensive sexual reproductive health rights (SRHR) services; social asset building interventions; school-based HIV and violence prevention; community mobilization and norms change; parenting/caregiver programmes.

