### Study design

This study is a single cross-sectional survey targeting 18,500 AGYW, to be conducted in 2017/2018 in four selected districts in South Africa. AGYW between 12 and 24 years will be selected using a stratified cluster-based sampling approach, with districts representing strata and the cluster or primary sampling unit being the small area layers (SALs). SALs were created by merging adjacent Enumeration Areas (EA), which had less than 500 people, to create a spatial area layer that corresponded as closely as possible to the EA layer. The following criteria were used for the establishment of the SALs. EAs were merged if they fell within the same sub-place (a higher order geographic level); EAs were merged if they had the same geographical properties; an EA was merged if its population that resided there was less than 500 people; and lastly, the resulting SALs must have a population total of 500 or more [37].

Stratified sampling was chosen as it reduces sampling error and ensures a greater level of representation when compared to simple random sampling [38]. It also ensures more precise estimates, provided that there is homogeneity within strata and heterogeneity between strata [38]. A questionnaire will be administered and biological samples collected (two micro-containers of blood for dried blood spot (DBS), plasma specimens and self-collected vulvo-vaginal swab samples (VVSS) to test for HIV infection, HIV incidence, STIs as well as pregnancy respectively).

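### The 'ART naïve' proportion in the first secondary objective cannot be identified from viral load and antiretroviral drug measurement, the only data named for it

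*Protocol article*

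**What the plan says.** The first secondary objective (Study objectives) is to measure HIV prevalence and the "proportion of HIV positive AGYW on ART and ART naïve with detectable and undetectable HIV-1 Ribonucleic Acid (RNA) viral load". It names two treatment groups and gives no place to women who started ART and stopped.

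Analysis of secondary objectives describes the derivation in two consecutive sentences that use different terms. The first says that the proportions on ART and "those not on ART who have detectable or undetectable viral loads will be determined through laboratory tests". The second says that HIV-1 viral load data and antiretroviral "drug measurement data will be used to determine the proportion of HIV infected persons on ART and ART naïve with detectable and undetectable" viral loads. No other data source is named there for treatment status.

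Under Data collection, the questionnaire's items on health-seeking behaviour include "HIV treatment (initiation date". The analysis text does not link this item to the ART classification.

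**The concern.** 'Not on ART' and 'ART naïve' are different quantities. The first is a state on the day of sampling; the second is a statement about the whole of a woman's past. The text moves from one to the other without adding any information about the past.

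Two results are at stake. One is the naïve share itself: a woman who started treatment and stopped would be reported as never having started. The other is the detectable/undetectable split within the naïve group, which would mix never-treated women with former users.

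The distinction matters to this evaluation. Linkage to care is one of the DREAMS components, and the Discussion says the results should help identify the interventions that most increase uptake of ART. Not starting treatment and not staying on it are different programme failures.

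**Working it through.** The plan states no figure for the ART-naïve share, so there is nothing to reproduce. The check is mainly one of definition.

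**Step 1: what the named data can show**

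| Woman's true status | Drug result | Viral load |
|---|---|---|
| Taking ART | normally detected | often suppressed, may be detectable |
| Started ART, now stopped | not detected | may be detectable or, for a time, not |
| Never treated | not detected | usually detectable, not always |

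The second and third rows share the same drug result, and their viral loads overlap. No rule built on these two measurements alone can separate them. A group formed from them is 'no drug detected', which matches 'not on ART' and not 'ART naïve'.

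**Step 2: direction.** Let u be the share of HIV-positive participants with no drug detected, and s the fraction of those who had ART before. If the no-drug group is labelled naïve:

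- labelled naïve share = u
- true naïve share = u × (1 − s)
- excess = u × s

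The excess is zero only if no woman without detected drug was ever treated. Through this mechanism it cannot be negative.

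**Step 3: size, as an illustration only.** From the document: a target of 18,500 participants (Study design) and a planning prevalence of 25% (Statistical considerations and sample size calculation). Expected HIV-positive: 18,500 × 0.25 = 4,625. The document gives neither u nor s. Assumed ranges are u = 30–70% and s = 0–30%.

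| u | s | Labelled naïve | Truly naïve | Excess (points) | Women, about |
|---|---|---|---|---|---|
| any | 0% | u | u | 0 | 0 |
| 30% | 10% | 30% | 27% | 3 | 139 |
| 50% | 10% | 50% | 45% | 5 | 231 |
| 50% | 20% | 50% | 40% | 10 | 462 |
| 70% | 30% | 70% | 49% | 21 | 971 |

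For the third row: 0.50 × 0.10 = 0.05, and 4,625 × 0.05 ≈ 231.

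**Step 4: the viral load split.** The undetectable share reported for the 'naïve' group would be (1 − s) × p₀ + s × p₁, where p₀ is that share among never-treated women and p₁ among former users. It is distorted to the extent that p₀ and p₁ differ. The document gives neither, so even the direction of this second error is open.

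**The case against.** The strongest reply is that no sentence says drug-negative means naïve. The text says the two laboratory measures will be used; it does not say that nothing else will be, nor that the two groups cover every HIV-positive participant. A previously treated group outside both would be compatible with the wording. The article condenses a fuller protocol, the initiation date is collected, and the derivation may use it. On the kindest reading, 'those not on ART' is the operative class and 'ART naïve' is loose wording, in which case the estimates stand and only a label is wrong.

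Much of this holds. The assignment rule is inferred from three things: the two named categories, the two named data sources, and the use of both terms in adjacent sentences for what appears to be one group. The magnitude is wholly assumed.

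It does not remove the point. Whether or not the two groups are exhaustive, the article says which data will determine the naïve proportion, and those data cannot do so. That is an error in what is stated, not a detail left for later. If 'not on ART' is the intended class, the objective still promises a different quantity.

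A reader might infer more: that the plan fixes a misclassification rule, that the naïve share is inflated by a known amount, or that the primary incidence estimate is affected. The documents support none of these. The rule is not written out, no discontinuation or drug-detection figure is given, and nothing shown links this label to the LAg-based estimate of the primary outcome.

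**Conclusion.** The point holds as a mismatch between a stated quantity and the data stated to produce it. Viral load and drug measurement identify current or recent drug use, not treatment history, and the analysis text itself uses the current-use term one sentence earlier.

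If the group is formed as the text implies, the naïve share is overstated by u × s. That conclusion assumes that 'no drug detected' is what becomes 'naïve', and that at least some of these women were treated before. The document does not allow the amount to be estimated; the 0 to 21 points above reflect only the assumed ranges.

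The consequence is confined to a descriptive secondary outcome. It should be corrected because it changes what the first secondary objective reports and is easy to put right.

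**What to change.** In Study objectives and in Analysis of secondary objectives, replace 'ART naïve' with 'no ARV detected (not on ART)' for the laboratory-defined group. Then use the questionnaire's treatment initiation date to report three classes, with viral load in each:

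1. ARV detected (on ART)
2. No ARV detected, prior ART reported
3. No ARV detected, no ART reported

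The third class should keep that descriptive name and not be called naïve, because women who do not disclose past treatment remain in it. If the questionnaire item is not used, the renaming alone makes the claim match the data.

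The cost is a wording change in two sections and one derived variable from an item already collected. No new data, testing or sample size is needed. The downside is that the split between classes 2 and 3 rests on self-report, which may be incomplete and should be stated beside the result.
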